### Interventions

In the taVNS group, a taVNS device will be used (Hwato, SDZ-IIB, Suzhou, China) to stimulate the auricular branch of the vagus nerve distribution area located posterior and inferior to the external auditory meatus, with clear anatomical localization. The stimulation parameters will be as follows (31, 32): (1) dense-sparse waves with a pulse frequency of 4/20 Hz; (2) current intensity of 3–14 mA, individually adjusted according to the patient’s tolerance; (3) stimulation time of 30 min per session. Patients will be placed in a comfortable position. The treatment will be administered once daily, five days per week, for a total of four weeks. These parameters were chosen on the basis of our team’s previous taVNS trials in primary insomnia and depression, in which the same dense-disperse 4/20 Hz waveform and 30-minute daily session produced clinical benefit with good safety and tolerability (15, 31, 32). The auricular branch of the vagus nerve distribution was selected as the stimulation target because this region is densely innervated by vagal afferent fibers, enabling direct, non-invasive activation of the vagal pathway. The current intensity will be individually titrated within the 3–14 mA range to the highest level that evokes a distinct but non-painful tingling sensation, so as to ensure adequate afferent activation while maintaining tolerability and minimizing the risk of adverse effects (10). The 4-week course was set to match the intervention duration shown to be effective in our prior insomnia studies and to align with the typical timescale of post-stroke neuroplastic change.

In the sham-taVNS group, the same therapeutic device will be used, but the stimulation site will be the superior scaphoid fossa at the midpoint of the external auricular margin, an area not innervated by the vagus nerve (**Figure 2**). The selection of this site as the sham target is supported by authoritative anatomical evidence. In the classic cadaveric dissection of the human auricle, the auricular branch of the vagus nerve was found to innervate the cymba conchae (100%), the cavity of concha, and the tragus, whereas the scapha and scaphoid fossa receive their cutaneous innervation from the great auricular and auriculotemporal nerves rather than the vagus nerve (33). Accordingly, the superior scaphoid fossa lies outside the vagal innervation territory and is not expected to activate central vagal afferent pathways. Consistent with this anatomy, the scaphoid fossa has been adopted as a non-vagal sham site in previous double-blind, sham-controlled taVNS trials, in which stimulation of this region produced comparable tactile sensation without engaging the vagal pathway (34). The stimulation parameters and treatment course will be the same as those in the treatment group.

**Figure 2 f2:**
[figure not shown]
Stimulation sites for taVNS and sham taVNS. The green area indicates the auricular branch of the vagus nerve distribution.

### Basic treatment

During the 4-week intervention period, all participants will receive standard basic treatment, including conventional post-stroke medication and rehabilitation training. Medication will be administered in accordance with the *Chinese Guidelines for the Diagnosis and Treatment of Acute Ischemic Stroke 2023* (35). Rehabilitation training will include functional training, routine medical care, and other standard rehabilitation procedures.

To avoid potential confounding effects on sleep outcomes and multimodal MRI indicators, sedative-hypnotic drugs will not be routinely prescribed during the study period. Estazolam will be permitted only as rescue medication when participants experience severe or intolerable insomnia, such as inability to sleep for two consecutive nights or when clinically judged necessary by the investigator. The recommended rescue dose will be estazolam 1 mg orally before bedtime. The use of rescue medication, including dosage, frequency, and timing, will be recorded in detail throughout the study. Participants will be instructed to avoid taking estazolam within 48 hours before MRI scanning and clinical assessments whenever clinically feasible.

### Multimodal MRI data acquisition

All multimodal MRI data will be acquired on a Siemens 3.0T Vida scanner at the Shunyi Hospital of Beijing Hospital of Traditional Chinese Medicine. For each participant, scanning will be performed at two time points: on the day before the first treatment session and on the day after completing the 4-week intervention. To minimize variability, all scans will be obtained using identical hardware, sequences, and acquisition parameters at both time points.

Three sequences will be acquired in a fixed order. First, resting-state functional MRI (rs-fMRI) will be obtained using a gradient-echo echo-planar imaging (GRE-EPI) sequence to capture spontaneous neural activity. During the scan, participants will be instructed to remain awake with their eyes closed, stay as still as possible, and refrain from engaging in any structured thought. Next, a three-dimensional T1-weighted image (3D-T1WI) will be acquired to provide high-resolution structural information for morphometric analysis and for spatial normalization of the functional and perfusion data. Finally, arterial spin labeling (ASL) perfusion imaging will be performed to quantify cerebral blood flow. The detailed acquisition parameters for all three sequences are summarized in **Table 1**.

**Table 1 T1:** Acquisition parameters of the multimodal MRI sequences.

Parameter	rs-fMRI (GRE-EPI)	3D-T1WI	ASL
Repetition time, TR (ms)	2000	2530	4200
Echo time, TE (ms)	30	2.98	38.06
Flip angle, FA (°)	90	7	120
Field of view, FOV (mm)	224 × 224	256 × 256	224 × 224
Matrix	64 × 64	256 × 256	64 × 64
Slice thickness (mm)	3.5	1.0	3.5
Number of slices	32	192	46
Voxel size (mm³)	3.5 × 3.5 × 3.5	1.0 × 1.0 × 1.0	3.5 × 3.5 × 3.5
Number of time points	200	—	—
Acquisition time	6 min 46 s	6 min 3 s	7 min 21 s

rs-fMRI, resting-state functional MRI; GRE-EPI, gradient-echo echo-planar imaging; 3D-T1WI, three-dimensional T1-weighted imaging; ASL, arterial spin labeling; TR, repetition time; TE, echo time; FA, flip angle; FOV, field of view.

### Outcome measures

#### Primary outcomes

The primary outcomes include neuroimaging indicators derived from fMRI, 3D-T1WI, and ASL, specifically: The primary outcome is defined as the change in these multimodal MRI indicators from baseline to the end of the 4-week intervention; the principal comparison is the between-group difference in these changes (taVNS vs. sham-taVNS), with within-group pre-to-post changes assessed as a secondary contrast. The specific indicators are as follows:

##### fMRI

###### Amplitude of low-frequency fluctuation and fractional amplitude of low-frequency fluctuation

ALFF effectively reflects spontaneous neural activity in the cerebral cortex by calculating the average amplitude of low-frequency signal fluctuations, and is a commonly used method for analyzing signal characteristics of individual voxels or localized brain regions (36). This metric has been widely applied in studies of spontaneous brain activity under various conditions (37). fALFF is an improved analytical method based on ALFF. It effectively reduces the susceptibility of ALFF to physiological noise interference in the cerebral pool and ventricular regions, offering higher sensitivity and specificity for the detection of spontaneous brain activity (38).

###### Regional homogeneity

ReHo is based on Kendall’s coefficient of concordance and evaluates the similarity between a target voxel and its neighboring voxels over a time series on a voxel-by-voxel basis (39). This method is widely used in the analysis of changes in local spontaneous neural activity in neuropsychiatric disorders, as well as in studies of the central mechanisms of taVNS (40).

###### Functional connectivity

FC refers to the temporal synchrony between distant neurons or brain regions during rest. It is typically measured by calculating the temporal correlation coefficients of BOLD signals across different brain regions, reflecting functional integration and information exchange between brain regions (41, 42).

##### 3D-T1WI

###### Gray matter volume

GMV is one of the most widely used indicators derived from 3D-T1WI structural imaging. Through the VBM pipeline, the acquired T1-weighted images are segmented into gray matter, white matter, and cerebrospinal fluid (CSF) tissue maps, which are then spatially normalized and modulated to enable voxel-wise comparison of regional GMV across subjects (43). GMV reflects the density and integrity of neuronal cell bodies, dendrites, and synapses within a given brain region, serving as a sensitive marker for detecting neurodegenerative and neuroplastic changes (44).

###### Cortical thickness

Cortical thickness (CT) is a key morphometric indicator obtained through SBM analysis. Unlike VBM, which operates in volumetric space, SBM reconstructs the cortical surface by identifying the boundary between Gray Matter (GM) and white matter and the boundary between GM and CSF, and then calculates the shortest distance between the two surfaces at each vertex (45). CT is considered a sensitive biomarker reflecting cortical cytoarchitecture, columnar organization, and myelination status, and has been shown to be influenced by aging, neurodegeneration, and experience-dependent plasticity (46).

###### Cortical surface area

Cortical Surface Area (CSA) is another important morphometric parameter derived from SBM analysis. It measures the total area of the cortical mantle at each vertex and is closely related to the tangential expansion of cortical columns during neurodevelopment (47). Unlike cortical thickness, which primarily reflects radial growth and dendritic arborization, CSA is thought to be largely determined by the number of cortical minicolumns and is influenced by distinct genetic and environmental factors (48).

##### ASL

###### Cerebral blood flow

CBF is the core quantitative parameter obtained through arterial spin labeling imaging. It represents the volume of blood delivered to a unit mass of brain tissue per unit time and directly reflects local cerebral perfusion status and metabolic demand (49, 50). Through neurovascular coupling mechanisms, cerebral blood flow is closely associated with local neuronal activity: increased neuronal activity induces local vasodilation, leading to a corresponding increase in blood supply to meet the elevated metabolic demands of active neurons (51). Therefore, CBF serves as both a reliable surrogate marker of local cerebral metabolism and an effective indicator of the integrity of neurovascular coupling.

#### Secondary outcomes

Secondary outcome measures include efficacy-related scales, specifically the Pittsburgh Sleep Quality Index (PSQI), the National Institutes of Health Stroke Scale (NIHSS), the Activities of Daily Living (ADL) assessment scale, the 17-item Hamilton Depression Rating Scale (HAMD-17), and the 14-item Hamilton Anxiety Rating Scale (HAMA-14). These scales will be assessed once each at baseline (Week 0), Week 2, and Week 4 of treatment. The PSQI is the principal secondary endpoint, reflecting subjective sleep quality, while the NIHSS, ADL, HAMD-17, and HAMA-14 are supportive secondary endpoints capturing neurological function, daily living ability, and depressive and anxiety symptoms, respectively. For each scale, the between-group difference in the change from baseline and the time course across the three assessment points (Week 0, Week 2, and Week 4) will be evaluated. In addition, the use of rescue medication, including the number of nights and total dose of estazolam, will be recorded as an exploratory outcome.

The PSQI is used to assess sleep quality in post-stroke patients. This scale is widely used in clinical research, has good reliability and validity, and can effectively distinguish between different groups with sleep disorders (52). The NIHSS is a simple, rapid, and effective tool for assessing neurological deficits following stroke. It exhibits high intra- and inter-rater reliability and is widely used both domestically and internationally to evaluate the severity of neurological deficits and disease progression (53). The ADL assessment scale is used to evaluate the ability of post-stroke patients to live independently. It covers basic daily activities such as eating, dressing, and toileting, and can objectively reflect the level of functional recovery and the effectiveness of rehabilitation treatment (53). The HAMD-17 is used to assess the severity of depressive symptoms in post-stroke patients. It is one of the most commonly used depression assessment tools in clinical research and demonstrates good internal consistency and inter-rater reliability (54). The HAMA-14 is used to assess the severity of anxiety symptoms in post-stroke patients. It effectively reflects changes in anxiety status, possesses good reliability and validity, and is suitable for clinical efficacy assessment (55).

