### Inclusion criteria

(1) Confirmed by MRI and meeting the diagnostic criteria for ischemic cerebrovascular disease; (2) Aged between 40 and 80 years, regardless of gender; (3) Insomnia first occurring more than 2 weeks after acute stroke, with no prior history of insomnia; (4) Pittsburgh Sleep Quality Index (PSQI) score > 7; (5) Conscious and able to cooperate with all scale assessments; (6) Voluntary participation in the study, signing the informed consent form, and committing not to participate in other clinical studies during the treatment period.

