Such integrated analyses are expected to identify specific neuroimaging biomarkers that can not only predict treatment responsiveness but also clarify the central mechanisms through which taVNS exerts its therapeutic effects. For example, the association between enhanced functional connectivity in the DMN and reduced PSQI scores may suggest that taVNS exerts its sleep-promoting effects by modulating large-scale neural networks involved in self-referential processing and arousal regulation (70). Similarly, the correlation between increased cerebral blood flow in the thalamus and prefrontal regions and improved sleep maintenance may indicate that the restoration of neurovascular coupling is one of its key mechanisms of action (71). Building on these prior mechanistic findings, we can make several specific predictions regarding the brain regions most likely to be modulated by taVNS in PSI. At the functional level, given that taVNS has been shown to normalize spontaneous activity and to enhance connectivity within the default mode network, thalamus, and prefrontal cortex in primary insomnia and depression (17, 40, 70), we anticipate that the taVNS group will show increased ALFF/fALFF and ReHo in the prefrontal cortex and precuneus, together with strengthened thalamo-cortical and intra-DMN functional connectivity. At the structural level, because chronic sleep deprivation is associated with gray matter atrophy in the hippocampus, prefrontal cortex, and anterior cingulate cortex (24, 25), a 4-week intervention may produce measurable increases, or attenuated loss, of gray matter volume and cortical thickness in these emotion- and cognition-related regions. At the perfusion level, taVNS is expected to increase cerebral blood flow in the thalamus and prefrontal cortex, reflecting restored neurovascular coupling in hypoperfused, sleep-regulating areas. We further hypothesize that these regional changes will correlate with clinical improvement, such that greater enhancement of prefrontal-thalamic function and perfusion is accompanied by larger reductions in PSQI and HAMD/HAMA scores. Specifying these candidate regions and directional hypotheses in advance strengthens the forward-looking value of the protocol and provides concrete, testable targets for the planned analyses.

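### HAMD-17 and HAMA-14 totals partly measure sleep (assuming the standard forms), so a sleep-only effect can carry over in part to the mood endpoints; prespecify companion scores without the insomnia items

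*Protocol article*

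**What the plan says.** The Secondary outcomes section gives each scale a construct. For sleep: "The PSQI is the principal secondary endpoint, reflecting subjective sleep quality". For the rest: "while the NIHSS, ADL, HAMD-17, and HAMA-14 are supportive secondary endpoints capturing neurological function, daily living ability, and depressive and anxiety symptoms, respectively". Each scale is then analysed on its own: "For each scale, the between-group difference in the change from baseline and the time course across the three assessment points" will be evaluated.

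The Imaging data analysis section correlates changes in the imaging metrics with changes in each of the five scales. It does this within each arm and with Bonferroni correction.

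The Discussion predicts that "greater enhancement of prefrontal-thalamic function and perfusion is accompanied by larger reductions in PSQI and HAMD/HAMA scores".

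Entry requires a "Pittsburgh Sleep Quality Index (PSQI) score > 7". The inclusion criteria set no minimum on either Hamilton scale, and the exclusion criteria remove only severe psychiatric illness.

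The article does not list the items of either Hamilton scale, does not mention their overlap with sleep, and describes no score without sleep items.

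**The concern.** If the two Hamilton scales contain insomnia items, their totals are not pure measures of mood and anxiety. That matters more here than in most trials, because every participant enters with disturbed sleep and the treatment is aimed at sleep. Suppose taVNS improved sleep and left mood and anxiety unchanged. The insomnia items would still fall more in the taVNS arm, and the totals would fall with them. Under the plan's labels, that fall would be reported as a change in depressive or anxiety symptoms.

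The correlations have the same weakness. An imaging change that tracks sleep would correlate to some degree with HAMD-17 change through the shared items, and the Discussion's joint prediction for PSQI and HAMD/HAMA would look better supported than it is. The introduction links post-stroke insomnia to later anxiety, and the abstract adds depression, so readers are likely to take a Hamilton difference as a separate benefit.

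**Working it through.** **Inputs from the protocol.** 24 participants per arm (Sample size calculation); two-sided 5% level (Clinical data analysis). The protocol gives no effect size, SD or power for any scale, so there is no figure of its own to reproduce.

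**Assumptions, not in the protocol.**
- HAMD-17: three insomnia items scored 0–2, up to 3 × 2 = 6 points of a maximum of 52.
- HAMA-14: one insomnia item scored 0–4, of a maximum of 14 × 4 = 56.
- SD of change in the total: 3 to 6 points.
- Between-group difference arising from the insomnia items alone: 1, 2 or 3 points on HAMD-17; 0.5 or 1 point on HAMA-14.
- All 24 per arm analysed, by a two-sample t-test on change. The plan also names repeated-measures ANOVA; the t-test is the simpler stand-in.

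**Share of the score range.** 6/52 = 11.5% for HAMD-17 and 4/56 = 7.1% for HAMA-14. The share of the observed baseline total could be higher or lower; no baseline scores are given.

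**Chance of a nominally significant total when only sleep changes.** Let δ be the sleep-only difference. The noncentrality is (δ/SD) × √(n/2) = (δ/SD) × √12, with 2 × 24 − 2 = 46 degrees of freedom and critical value 2.013. Example: δ = 2, SD = 3 gives 0.667 × 3.464 = 2.309, and the noncentral t gives 0.62.

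| Scale, sleep-only difference | SD 3 | SD 4 | SD 5 | SD 6 |
|---|---|---|---|---|
| HAMD-17, 1 point | 0.20 | 0.14 | 0.10 | 0.09 |
| HAMD-17, 2 points | 0.62 | 0.40 | 0.27 | 0.20 |
| HAMD-17, 3 points | 0.92 | 0.72 | 0.53 | 0.40 |
| HAMA-14, 0.5 point | 0.09 | 0.07 | 0.06 | 0.06 |
| HAMA-14, 1 point | 0.20 | 0.14 | 0.10 | 0.09 |

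The reference value with no overlap is 0.05. A 2-point HAMD-17 difference is one third of the 6-point insomnia range and a 3-point difference is half of it, in each case over and above sham, so the lower rows for HAMD-17 describe large sleep effects.

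**Correlations.** Write the HAMD-17 change as S + R, where S is the change on the insomnia items and R the change on the other items. For an imaging change I, Cov(I, S + R) = Cov(I, S) + Cov(I, R). If I tracks sleep only, the second term is zero and the first is not, so the correlation with the total is not zero either.

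**With the insomnia items removed.** A sleep-only effect moves R by 0, so the chance of a significant result returns to 5% and Cov(I, R) is 0.

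**The case against.** The item content is not in the protocol. That stands, and the point is therefore conditional. It concerns the make-up of instruments the protocol itself names, and the sponsor can confirm it from the forms in use.

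Using the full total of a named scale is ordinary practice, and a sensitivity score may sit in an analysis plan that is not shown. Also true, so the absence of such a score is not an error. What remains is the construct the article itself gives to these totals and the Discussion's hypothesis built on it.

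A reader might infer that the plan counts the sleep benefit twice. The document does not support that: there is no composite or joint success rule, each scale is tested separately, and only the insomnia items carry over. A reader might also infer that a HAMD-17 or HAMA-14 difference could never be read as a mood or anxiety effect. That is too absolute, because the overlap is partial and its weight depends on the size of the sleep effect. Nor can one say that sleep items dominate the totals at entry: no baseline scores are given, and people with mild or moderate depression or anxiety may enroll.

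Finally, nothing in the protocol supports a 2- or 3-point sleep-item difference, and fewer than 24 analysed per arm would lower every figure in the table. Both are fair, and are why the 1-point row and SD 6 are shown.

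**Conclusion.** The point holds in a limited form. Assuming the standard forms, part of what the plan labels depressive and anxiety symptoms is sleep, in a sample chosen for poor sleep. For HAMD-17 this can matter: the chance of a nominal depression difference with no true mood effect is about 20–9% for a 1-point sleep-only difference, and 62–20% or 92–40% if the sleep effect is large (2 or 3 points). For HAMA-14 it is minor, close to nominal at half a point. These ranges rest on assumed SDs of 3 to 6 and 24 analysed per arm.

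Both scales are supportive secondary endpoints. No primary conclusion and no stated figure changes, and the PSQI comparison is unaffected. What changes is what may be concluded about mood and anxiety apart from sleep.

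**What to change.** In Secondary outcomes, keep the full HAMD-17 and HAMA-14 totals as the named supportive endpoints. Add two prespecified companion scores: HAMD-17 without its three insomnia items and HAMA-14 without its insomnia item. Analyse them in the same way as the totals and use them in the correlations described under Imaging data analysis. State that a mood or anxiety effect separate from sleep will be claimed only if the companion score supports it, and that the full totals will not be treated as evidence independent of the PSQI.

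The companion scores should not replace the totals: the reliability and validity that the protocol cites are for the full scales.

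Cost: no new visit, patient or instrument, provided the item scores are recorded and not only the totals; the article does not say which, so the case report form should be checked. The companion scores add a few analyses, are less familiar and carry no validation of their own. Any added correlations also enter the Bonferroni count.
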